### Data sources and measurement

Nurses previously trained to complete comprehensive geriatric assessments with the interRAI-HC and additional instruments will collect the data. On each measurement occasion, participants will receive the interRAI-HC, which provides the outcomes used to derive the frailty (FI) and complexity (CI) indices, and a life history calendar (LHC), which provides the outcomes used to assess the predictive validity of FI and CI.

The interRAI-HC, Canadian French version 9.1 (243 items, 90 min [38]) is a standardized comprehensive geriatric assessment that belongs to a suite of instruments designed for standardized assessment across settings [41] and for consistent information sharing [42]. Version 9.1 of the Canadian French interRAI-HC entails a minimal dataset (MDS) covering the following domains: administrative information (A) and living conditions (B), cognition (C), sensory abilities (D), health-related behavior (E) and social behavior (F), activities of daily living (ADL, G), continence (H), medical diagnoses (I), falls, physical abilities, physical symptoms and pain (J), nutrition (K), skin and feet problems (L), medication (M), ongoing therapies and formal care (N), advanced care instructions and legal representativity (O), informal care (P), living environment (Q), observed change in ADL (R) and record information (S). As previously demonstrated [28–32], the quality and nature of the information collected with the interRAI-HC will be rich enough to derive a variety of additional clinical scores and indices.

The life history calendar (LHC, 15 min [43]). The LHC is a retrospective method used to gather reasonably valid information on past events. The LHC allows for the fine-grained time-to-event recoding of events, and it appears to be well suited to documenting adverse outcomes. As designed for the fraXity study, the tool covers the 6 months preceding each interview. It will assess the history of falls, emergency admissions, hospitalizations and lengths of stays, physician visits and life-striking events (e.g. separation, relocation, death of kin, medical diagnosis).

Additional sociodemographic and health questionnaires will be used to document population characteristics; the choice of the instruments will follow the recommendations of the International Consortium for Health Outcomes Measurement (ICHOM) [44, 45].

The EuroQoL EQ-5D-3 L (six items, 5 min [46]) is used to evaluate self-perceived health-related quality of life.

The Mini Nutritional Assessment–Short Form (MNA-SF, seven items, 5 min [47]) is a standardized scale designed to evaluate the nutritional statuses of older adults.

The Montreal Cognitive Assessment (MoCA, 30 items, 20 min [48]) is used to evaluate global cognitive functioning.

Global health status will be assessed by means of an ad hoc questionnaire serving to document self-reported additional health outcomes that include visual and auditory difficulties, frailty status, fear of falling, pain, current pathologies, and alcohol and tobacco consumption. The questionnaire will serve to document the sample characteristics and complements the heath-related data collected with the interRAI-HC with external measures.

Sociodemographic status will be assessed by means of an ad hoc questionnaire that serves to document basic sociodemographic outcomes, including age, sex, educational and professional attainment, living arrangements, living conditions, social participation and caregiving, self-perceived isolation and loneliness, and overall satisfaction with life. The questionnaire will serve to document the sample characteristics and complements the sociodemographic data collected with the interRAI-HC with external measures.

At the end of each assessment, the COMID [37] will be used to assess the multidimensional complexity of the case/situation. It will serve as an external measure of complexity, which serves to assess the convergent validity of the CI derived from the interRAI-HC assessment.

### Primary outcome measures

The FI and the CI derived from the baseline interRAI-HC assessments will be the main primary outcome measures. These scale variables will hold a value ranging from 0 to 1.00, computed as the sum of items recorded with the interRAI-HC MDS divided by the number of items considered. Changes in FI and CI values across occasions will further be considered as additional primary outcomes. Changes will be expressed as a proportion, with the index value at baseline being the denominator and the observed index value at follow-up being the numerator.

### Secondary outcome measures

The events recoded by means of the LHC will the secondary outcome measures. They include the number of falls, hospitalization, physician visits, emergency admissions and deaths. They will be used to estimate the predictive validity of the FI and CI.

### Bias

Information bias will be addressed through the double-checking of the criteria used for group assignment, which are first identified based on information collected with the EQ and subsequently adjusted based on data collected at baseline with interRAI-HC. Furthermore, information bias will be addressed via statistically testing group differences on potential confounding variables, such as age, sex, education and living arrangement. Should group differences be significant (*p* < .05) on a given variable, the variable will be used as a covariate in subsequent analyses so as to control for its confounding effect. Selection bias, potentially enhanced by the convenient sampling method, is addressed at recruitment. Calls for participation will be sent out in all municipalities of the canton of Geneva to enhance the representativity of socioeconomic neighborhoods and environments (e.g. urban vs. rural). Furthermore, both public and private home service providers will relay calls for participation among their clients to enhance the representativity of care and service recipients. Interviewer bias, which challenges the quality of the data collected, will be addressed by providing specific training to the nurses in charge of data collection and prior field work. Training will focus on validity (appropriate knowledge of what each instrument actually measures), reliability (appropriate use of homogenous instructions in standardized questionnaires) and quality of data (avoiding missing values). Practice sessions were organized to ensure that the nurses properly master the measurement instruments prior to data collection. Finally, measurement bias will be addressed by using, whenever possible, standardized instruments with documented validity and/or reliability.

### Study size

At the end of the study, the target sample size will be 70 participants in each group, for a total of 210 participants. This sample size was determined using G*Power [49] applied to a multivariate analysis of variance (MANOVA) design assessing within-between interactions for three groups and three repeated measures, for an expected effect size of f(V) = .20, an α error probability of .05 and power (1-β error probability) of .90. The results provided a critical overall size of *N* = 195, which was raised to *N* = 210 so as to reach an equivalent sample size of *N* = 70 in each group. Provided the expected size at the end of the study, an estimated *N* = 325 initial contacts for each group was determined, using an initial response rate of 30% (*N* = 97 positive responses), a subsequent eligibility rate of 90% (*N* = 87 initial assessments) and a 10% attrition rate between measurement occasions (*N* = 78 at 6 months and N = 70 at 12 months).

### Statistical methods

Specific analyses are planned for assessing each objective of the study. In all cases, descriptive and inferential statistics will be used. A priori, the threshold for rejecting the null hypothesis will be *p* < .05, but more conservative thresholds of *p* < .01 or *p* < .001 could be applied if a) covariates are required in the analyses, or b) the sample size is smaller than expected. Additionally, for all analyses conducted using regression models, the 95% confidence intervals (95% CI) of estimated coefficients will be used, informing the effect size and the range of expected values in the population. The 95% CI will be used to interpret the results above and beyond the standard α error probability.

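### The optional cut of the significance level to .01 or .001 has no stated basis, is inconsistent with the .05 used for sizing, and would reduce power if invoked

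*Protocol article*

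**What the plan says.** The Statistical methods section names p < .05 as the a priori threshold for rejecting the null hypothesis. It adds that stricter levels (.01 or .001 in place of .05) "could be applied if a) covariates are required in the analyses, or b) the sample size is smaller than expected". It does not explain the two triggers, choose between the two stricter levels, or say which analyses they would govern. The same section keeps 95% confidence intervals for every regression model and says they will guide interpretation beyond the p-value.

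The Study size section uses a single alpha. The calculation is for a MANOVA "assessing within-between interactions for three groups and three repeated measures". The effect size entered is f(V) = .20, and the error rates are given as "an α error probability of .05 and power (1-β error probability) of .90". It gives N = 195, raised so that "the target sample size will be 70 participants in each group, for a total of 210 participants".

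The Bias section decides when covariates enter. If the groups differ at p < .05 on a potential confounder such as age, sex, education or living arrangement, "the variable will be used as a covariate in subsequent analyses so as to control for its confounding effect". The section on comparing groups repeats this rule for baseline sociodemographic and health variables.

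**The concern.** Neither trigger is an error-rate argument. A valid test that includes covariates, or that runs on fewer people, is already referred to a distribution that takes the model and the sample into account. Lowering alpha on top of that corrects nothing the plan has identified. Trigger (b) works against the study, because it makes the test stricter when a shortfall has already reduced power.

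Trigger (a) is likely to be met. The Participants section defines the three groups as lower, medium and higher risk. The covariate rule screens several baseline variables, and one significant difference is enough.

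Two things are at stake. The first is the power stated in the Study size section, which was worked out at .05 and nowhere recalculated at .01 or .001. The second is the decision rule. A Group × Occasion result of p = .03, in a model with covariates, could be called significant or not under the same protocol. At .01 or .001 the retained 95% intervals would no longer match the test: an interval could exclude the null beside a result declared non-significant.

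**Working it through.** **Inputs, all from the Study size section unless marked.** k = 3 groups; m = 3 occasions; f(V) = .20; alpha = .05; power = .90; target N = 210. The alternative alphas of .01 and .001 come from Statistical methods.

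**Formula.** Repeated-measures MANOVA, within-between interaction, Pillai trace, noncentral F:
- s = min(k − 1, m − 1) = 2
- df1 = (k − 1)(m − 1) = 4
- df2 = s(N − k − (m − 1) + s) = 2(N − 3)
- λ = N × s × f(V)² = N × 2 × 0.04 = 0.08N
- power = P(F′ with df1, df2, λ exceeds the 1 − alpha quantile of the central F)

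**Step 1: reproduce the plan's figure.** At N = 195, df2 = 2 × 192 = 384 and λ = 0.08 × 195 = 15.6. Power at alpha .05 is .9001, and 195 is the smallest N that reaches .90. The stated N is reproduced exactly.

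**Step 2: change alpha only.** At N = 210, df2 = 2 × 207 = 414 and λ = 16.8.

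| N | alpha .05 | alpha .01 | alpha .001 |
|---|---|---|---|
| 210 (target) | .923 | .793 | .547 |
| 195 (calculated minimum) | .900 | .750 | .490 |
| 180 (illustrative shortfall) | .872 | .701 | .431 |
| 150 (illustrative shortfall) | .795 | .584 | .311 |

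The last two sizes are assumptions. They show how trigger (b) compounds a shortfall and are not in the protocol.

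**Step 3: N needed to keep 90% power.** This is 263 at alpha .01 and 351 at alpha .001, against a target of 210. The gaps are 263 − 210 = 53 and 351 − 210 = 141 further completers.

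**Step 4: sensitivity to the formula.** The other common noncentrality, λ = df2 × f(V)², gives N = 198 at alpha .05. Power at N = 210 is then .919, .785 and .536, and the required sizes are 266 and 354. The conclusion does not depend on the variant.

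**The case against.** The rule is permissive. The a priori threshold is .05, in agreement with the sizing, and if the stricter levels are never used the stated power stands. A reader might infer that the plan has given up its 90% power. The text does not support that: power is lost only if the rule is invoked, and at .01 with N = 210 it is reduced to .79.

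Every permitted departure is conservative, so no single test exceeds a false-positive rate of .05 because of this rule. That is correct, and the point is not one of inflated type I error.

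Baseline imbalance and achieved N can both be known before the outcome associations are examined, so the threshold need not be chosen post hoc. This also stands in part. The protocol does not say the choice will be made after results are seen. It also does not say when the choice is made or by what criterion, so it leaves that possibility open.

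It would be too flat to say that covariates or a small sample can never disturb type I error. The planned survival models rest on large-sample tests, which can be anti-conservative with few events, and selecting covariates by a significance pre-test can disturb nominal error rates. The protocol gives neither reason, and an optional choice between .01 and .001 would be a crude remedy for either.

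The 95% intervals soften the consequence, because readers will see precision at the .05 level whichever threshold is used. They also sit awkwardly beside a .01 or .001 test.

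Finally, one might read the rule as a failed multiplicity correction. The protocol does not present it as one, and multiplicity across two indices and several outcomes is a separate matter that may be handled in an analysis plan not shown.

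**Conclusion.** The point holds in a limited form and should be fixed. The protocol contains a discretionary alpha rule with no stated rationale, which is inconsistent with the alpha used for sizing and with the 95% intervals. If it is invoked at N = 210, power for the Group × Occasion test falls by 13 percentage points at .01 (.923 − .793 = .130) or by about 38 at .001 (.923 − .547 = .376).

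These figures assume that f(V) = .20 is unchanged by adjustment. Prognostic covariates could recover some power and covariates correlated with group could cost more; the protocol gives no figure for either. They apply to the interaction that was sized, treated as the MANOVA of the Study size section, although the planned analysis is described as regression. No power is stated for the survival models or the baseline comparisons, so no stated power is lost there. That trigger (a) is likely is an inference from the risk strata and the covariate rule; the protocol gives no expected group differences.

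**What to change.** Delete the two conditional thresholds. State that alpha is .05 for all analyses, whatever covariates are included and whatever N is achieved. This matches the Study size section and the 95% intervals.

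If the team has a reason for a stricter level, it should state that reason, the level and the analyses covered before any outcome analysis, and revisit the sample size. For the sized test, 90% power needs N = 263 at .01 or N = 351 at .001.

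The deletion costs one sentence, with no new data and no burden on participants. It should be made before outcomes are analysed, because afterwards the choice of threshold cannot be shown to be independent of the results.

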### Deriving valid and reliable indices of frailty and complexity

The derivation of the frailty index (FI) will be done according to the methodology that Searle et al. [39] proposed and that the research group previously applied [32]. The methodology will be used as a scaffold to derive the CI. Descriptive analyses will be conducted to characterize the distributions of the FI and the CI. The reliability of the FI and CI will be estimated using test-retest reliability procedures.

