**Methods:**

The study will rely on a prospective observational case-control longitudinal study. Three samples of individuals aged 65 or older living in the community will be considered: recipients of formal home care (case 1), of formal home assistance (case 2) and individuals free of formal home services (controls). All participants will receive interRAI-HC assessments at three measurement occasions, separated by six-month intervals. Baseline assessments will serve to derive frailty and complexity scores. Follow-ups will serve to assess the predictive validity of the proposed indices and to estimate the intra-individual change in frailty and complexity. Group comparisons will serve to identify subgroups of the population for whom the screening of frailty and complexity appears to be the most relevant.

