### Objectives

The main purpose of the fraXity study is to develop frailty and complexity index computation algorithms based on the Canadian French version of the interRAI-HC [38]. The frailty index (FI) derivation relies on the available methodology [39]. This well-documented rationale [26–32], further supported by the operational definition proposed in the COMID [37], is used to derive the complexity index (CI). By relying on a prospective observational case-control longitudinal design, the study aims to assess the predictive validity of the proposed indices with respect to undesirable health outcomes (falls, emergency admissions, deaths) and health resource consumption (length of hospital stays, number of physician visits), monitored throughout the course of the study. Three measurement occasions will be used to estimate intra-individual change in frailty and complexity, as assessed with the proposed indices. Finally, by considering different subgroups of the aged population (see below), the study should provide estimates of frailty and complexity rates in a panel of the older population wider than the usual clinical population that interRAI instruments target. Overall, the fraXity study addresses four research questions. (1) Can frailty, respectively complexity, indices be derived from information collected during a comprehensive geriatric assessment done with the RAI-HC? (2) What is the predictive validity of frailty, respectively complexity, indices with respect to adverse health outcomes and health resource consumption? (3) What are the rates of frailty, respectively complexity, in various subsamples of the older population, and how do these rates change over time? (4) Which recommendations for best practices can be drawn from the findings to mount care strategies aimed at reducing the risks of adverse health outcomes related to frailty, respectively complexity?

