## Method

### Study design

The fraXity study relies on a case-control longitudinal design with three measurement occasions (baseline, follow-up 1 and follow-up 2), each separated by a six-month interval.

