### Procedure

The general procedure of the fraXity study is summarized in Fig. 1. Recruitment will start with the sending out of calls for participation using the distribution of flyers on various occasions (e.g. community events, public conferences, senior citizens’ association meetings), posts on intuitional websites and ads in local community journals. Efforts will be made to cover all municipalities of the canton of Geneva so as to enhance the representativity of the sample by reaching individuals living in various socioeconomic neighborhoods and environments (e.g. urban vs. rural). Home service professionals from private and public institutions operating in the area will also distribute flyers to increase opportunities to reach individuals who benefit from home services (assistance or care). Candidates volunteering to participate manifest their interest by contacting the research team by phone, by regular mail or by e-mail. Subsequently, the fraXity staff organizes a first phone appointment (first contact) for eligibility assessment.

The aim of the first contact will be to verify eligibility criteria, assign temporarily each participant to a group, arrange a first appointment for assessment upon verbal agreement for participation and, if needed, provide additional information on the study. A dedicated eligibility questionnaire (EQ) serves to guide the interview by reviewing all of the eligibility criteria and by documenting the types of care and assistance from which the respondent eventually benefits.

At the first meeting, the nurse in charge of the data collection will begin by ensuring that the participant provides his/her written informed consent for participation prior to any data collection. Participants can enroll in the study for a 12-month period, during which they receive three assessments: a baseline and two follow-ups. Assessments will take place at the participants’ homes unless a person prefers a different place. As a rule, the same nurse will follow the participant throughout the study. In the event of non-returns across measurement occasions, the nurses will document the reasons for such: withdrawal, out of sight, death. Whenever possible, the nurses will also record the motives for withdrawals. Deaths are to be documented from administrative records and/or information that the relatives provide.

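### A test-retest coefficient over the 6- and 12-month gaps mixes measurement error with the change the study sets out to measure, so it is a measure of stability and generally understates the reliability of the FI and CI

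*Protocol article*

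**What the plan says.** Under *Deriving valid and reliable indices of frailty and complexity*, the protocol article gives one method: "The reliability of the FI and CI will be estimated using test-retest reliability procedures". It names no interval, coefficient or subsample there.

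Both indices are computed from the interRAI-HC. The abstract states: "All participants will receive interRAI-HC assessments at three measurement occasions, separated by six-month intervals". *Study design* describes the occasions as "each separated by a six-month interval", and *Procedure* describes a 12-month enrolment "during which they receive three assessments: a baseline and two follow-ups". No short-interval repeat, retest subsample or second rater is described. On raters, *Procedure* says: "As a rule, the same nurse will follow the participant throughout the study".

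The same occasions serve to measure change. *Objectives* says: "Three measurement occasions will be used to estimate intra-individual change in frailty and complexity, as assessed with the proposed indices". *Primary outcome measures* adds: "Changes in FI and CI values across occasions will further be considered as additional primary outcomes". *Comparing groups with various risks of adverse outcomes* models the interaction of group and occasion, and *Study size* bases the sample size on it.

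**The concern.** Test-retest estimation treats every difference between two administrations as error. That is defensible when the interval is short enough for the true score to stay put. Here the shortest interval described is six months, in people aged 65 or older, two thirds of whom receive home services by design. The rest of the protocol treats differences over that interval as signal. The same variance cannot be true change in one analysis and unreliability in another unless a model divides it.

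Reliable computation algorithms are the first expected result in the article's *Discussion*, and this is the only reliability evidence it plans. Read at face value, a low coefficient could make a sound index look poor, and a reader could not tell an imprecise index from a precise one applied to people who changed.

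**Working it through.** **1. The plan's own figure.** The article gives no reliability value, target or retest sample size. The nearest checkable figure is the sample size for the interaction of group and occasion (*Study size*): three groups, three occasions, f(V) = .20, α = .05, power .90, N = 195.

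- df1 = (3−1)(3−1) = 4; df2 = 2 × (195 − 3 − 2 + 2) = 384; λ = 195 × 2 × .20² = 15.6.
- The noncentral F gives power .900 at N = 195 and .923 at N = 210.

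The figure is correct. It matters here because it shows that the study is powered to find differential change over the very intervals that would supply the retest.

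**2. What a retest correlation measures.** With uncorrelated errors, r = ρ × √(R1 × R2). R1 and R2 are the reliabilities at the two occasions, and ρ is the correlation of true scores between them. Only when ρ = 1, with no differing individual change, does r equal reliability. A shift shared equally by everyone leaves ρ at 1, so it does not affect Pearson's r, but it does lower an agreement ICC.

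**3. Illustrative size.** The article gives no variance of the indices or of their change, so everything in this step is assumed.

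*Individual change independent of baseline.* True-score SD is 1, reliability R = .90, error variance ve = .10/.90 = .111, and c is the SD of individual true change. Then r = 1/√[(1 + ve)(1 + c² + ve)].

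| c | 6-month r |
|---|---|
| 0 | .90 |
| .3 | 1/√(1.111 × 1.201) = .87 |
| .5 | 1/√(1.111 × 1.361) = .81 |
| .7 | 1/√(1.111 × 1.601) = .75 |

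With a mean change of 0.2 SD as well, the agreement ICC is .88, .85, .80 and .73 in the same order.

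*Constant true-score correlation per interval (lag-1 change).* With R = .90 and stability .80 to .95, the 6-month r runs from .90 × .80 = .72 to .90 × .95 = .855. At stability .85 it is .765 at 6 months and .90 × .85² = .65 at 12 months.

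Taken together, an assumed .90 appears as about .72 to .87 at 6 months.

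**4. Can three waves separate the two?** Under lag-1 change with independent errors, r12 × r23 / r13 returns the reliability. In the example, .765 × .765 / .650 = .90. This is an identity under that model and does not test it. Suppose instead that individuals follow steady slopes (T, T + S, T + 2S, with S of SD c and independent of T). The ratio then becomes (1 + 2c²)/(1 + c² + ve):

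- c = .3: 1.18/1.201 = .98, where the true second-wave reliability is 1.09/1.201 = .91.
- c = .5: 1.50/1.361 = 1.10, where the true value is 1.25/1.361 = .92.

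So the simple ratio can overstate reliability and even exceed 1.

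**5. Precision.** I simulated normal data under the lag-1 model with reliability .90 and stability .85. The ratio has a 95% range of about .82 to .99 at N = 210 and about .75 to 1.06 at N = 70. A single group is too small; the pooled sample is usable.

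**The case against.** The strongest reply is that the disputed analysis is inferred. The section speaks only of test-retest procedures, in the plural, and names no interval or coefficient. A fuller protocol could hold a short-interval repeat or a three-wave estimator. That stands as a limit on certainty: no particular coefficient is fixed by the text. It does not remove the point, because the article does fix the number and spacing of assessments per participant, and a retest within that schedule can only span 6 or 12 months. If a short-interval repeat exists, one sentence would settle the matter.

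Several stronger readings are tempting, and the document does not support them:

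- *The coefficient equals reliability times stability, so the bias is known.* The product form needs equal reliability at both occasions and uncorrelated errors; squaring the stability term at 12 months also needs lag-1 change. Carry-over from the same nurse could push the coefficient up. No input for the size of the bias is in the article.
- *Reliability will differ between groups because one group changes more.* No reliability by group is planned, and no variance of change is given.
- *The three-wave ratio recovers the truth.* Only under its own model, as the steady-slope case shows.
- *Using the same nurse and only those who return are faults in themselves.* Holding the rater constant is normal for a retest, every retest uses people who were retested, and a comparison of dropouts is planned. The first point limits what may be claimed about between-nurse error, and no more.
- *Restricting to people with no recorded change in daily activities would give a clean check.* That selects on the instrument that yields the indices and can inflate agreement.

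It is also fair that reliability is neither a primary nor a secondary outcome, and that the likely error is conservative.

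**Conclusion.** The point holds at moderate severity. Followed as described, the plan gives a coefficient that mixes error with true change, and the protocol itself expects and tests that change. It generally understates reliability. The direction rests on individuals changing by differing amounts and on errors being essentially uncorrelated between visits. The size is not known from the document; the .72 to .87 for an assumed .90 is an illustration only. It would be wrong to conclude that the study's main analyses are compromised: the survival models, the group regressions and the sample size do not use this coefficient. What is affected is the claim that the algorithms are reliable.

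**What to change.** 1. Report the 6- and 12-month coefficients as stability, or as a likely lower bound for same-rater reliability, and name the coefficient used.
2. Estimate reliability from the three existing waves, pooled over groups, with a bootstrap interval. Use a quasi-simplex model as the main analysis and a random-slope (growth) model as sensitivity analysis, and show both. Do not rely on r12 × r23 / r13 alone.
3. State the assumptions: equal error variance or equal reliability across waves, the form of change, and uncorrelated errors even though the same nurse usually returns.
4. State that between-nurse reliability is largely not assessed.

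The cost is analysis wording, with no new visits. The downsides are a wider interval than for a plain correlation, dependence on the model (three waves give little or no room to test it), and reliance on participants seen at 12 months, planned as 70 per group against 78 at 6 months.
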